#### *1.5 How will the results of this trial be used?*

The results of this project will help policy makers who are deliberating about what access Canadians should have to medications. Medications are currently provided to outpatients in other developed countries where healthcare services are publicly funded. In Canada, strong economic and social justice arguments have been made for providing medications without charge [1], but this has not yet happened. This study will provide empirical evidence related to prescribing patterns, medication adherence, health outcomes and costs, and will provide evidence in support of national pharmacare if the results are positive.

#### *1.6 Describe any risks to the safety of participants involved in the trial.*

Patients in the intervention group will have improved access to the medications on the list of essential medications but retain their usual access to all medications (i.e., they can choose to pay for medications that are not on the list). Thus access is not reduced for any medications.

In addition to the usual risks associated with all medications that will be experienced by participants in both the control usual care group and the intervention group, participants in the intervention group are at risk of being exposed to or experiencing:

- i. Errors in switching to medications on the list of essential medications
- ii. Dissatisfaction with the new medications
- iii. Discontinuation effects of medications at the conclusion of the study

The risk of medication errors will be mitigated by having the pharmacist receiving the prescribed medication order review the electronic medical record which includes the history of medications previously prescribed. The pharmacist will use defined daily doses (DDD) defined by the WHO, which is a widely accepted standard for converting doses of equivalent

medications (these types of substitutions are currently routine for hospitalized patients).[32] The patients will also be contacted about the change in medications. Errors will thus only effect the medications taken by patients if they are made by prescribers and missed by both the pharmacist and the patient. Medication errors will be monitored by the Data and Safety Monitoring Board (DSMB).

In some cases, patients will be switched from brand name to generic products. Despite clear evidence that generics and brand name medications have similar clinical effects [33, 34], there is a perception by some that generics are inferior.[35] A RCT of “apparent” drug substitution (all pills were placebos) found that switching participants to placebos labeled as generic from branded placebos was associated with increased side effects such as dizziness, headache and dry mouth.[36] Medication adverse effects will be monitored by the DSMB.

At the conclusion of the study, participants in the intervention group will revert to their usual access to medications. In some cases participants will continue to access their medications while other participants will experience cost-related nonadherence after the conclusion of the trial. There are potential harms of stopping certain medications that have withdrawal symptoms (e.g antidepressants). Patients will be made aware of this possibility before they enroll in the study, before they start the medications and at the end of the trial. We will provide clinicians with instructions about how to manage patients who experience discontinuation effects, which usually resolve spontaneously. Discontinuation effects will be reported as medication adverse effects.

## ***2. The Proposed Trial***

### ***2.1 What is the proposed trial design?***

This will be an open label, parallel two arm, superiority, individually randomized controlled trial with 1:1 allocation.

### ***2.2 What are the planned trial interventions?***

The experimental intervention is conveniently providing essential medications to patients at no charge (see [cleanmeds.ca](http://cleanmeds.ca) for the list of medications). Both intervention patients and their prescribing clinicians will have access to the list of essential medications. Clinicians may prescribe new medications from the list of essential medications and patients may be switched to a listed medication (e.g from an unlisted ACE inhibitor to a listed one). Patients will receive listed medications at no charge. Patients may still be prescribed other medications and access them in the usual way (e.g. by paying for them). All prescriptions must be entered into the EMR by clinicians.

Medications that need to be started in a timely fashion (e.g. antibiotics) will be available at the clinic. Long term medications will be dispensed by a clinical pharmacist who has direct access to patient electronic medical records and prescriptions. If the pharmacist disagrees or requires clarification they must contact the clinician before proceeding to dispense the medication by mail. The study pharmacist will have access to EMR records of all three sites and medications will be mailed from the partner pharmacy in Toronto. Where necessary, medications can be mailed from partner pharmacies of the rural sites with coordination from the study pharmacist. These medications will be mailed with a default frequency of every 90 days, but alternative frequencies can be employed. At the discretion of the trial participant’s clinician and pharmacist the mailing frequency may be adjusted. The patient’s needs and medication will govern adjustments. For example, medications with a short shelf life may need to be mailed out more

frequently (ex: once a month). Controlled substances (e.g. opioids, sedatives, and stimulants) will not be included in the intervention for safety reasons and patients will access them in the usual fashion. Medications that cannot be mailed, must be picked up at the clinic or community partner pharmacies of the three sites.

After shipment, the pharmacist who will have access to interpretation services in 200 languages will call to counsel patients about their medications. For medications that cannot be counseled over telephone, these will be provided in partner pharmacies or clinic where pharmacists will counsel the patients in their use (e.g. IUDs, inhalers, insulin injections). Patients without a permanent address may choose an address (e.g. the clinic or a support centre) and those without a telephone may call the pharmacist for information about medications (e.g. from the clinic). Patients who are unable to communicate over the phone will be eligible for visits from the pharmacist. Home visits will be conducted in rural sites by local family health team staff in line with usual practice.

Other potential prescribers outside of the clinic (e.g. consultants) will be faxed a letter with the list of essential medications and patients will be provided with a card with information about the list that can be shared with other providers. Both communications will include contact information for the study pharmacist.

The control condition is usual care with usual access to medications and dispensing.

### *2.3 What are the proposed practical arrangements for allocating participants to trial groups?*

This is a double arm RCT at one urban and two rural sites. A randomization schedule for each site will be generated by computer to ensure allocation concealment. After a participant has provided informed consent, the site research coordinator will allocate the patient to one of the two groups using the allocation sequence from a computer generated random sequence.

### *2.4 What are the proposed methods for protecting against sources of bias?*

The investigators and analysts will be blinded to treatment allocation to reduce ascertainment bias. Patients, clinicians and pharmacists must know the arm of allocation. An intention-to-treat analysis will be employed.

Contamination in this trial is unlikely for the long term prescription medications in this trial. These are the medications most commonly associated with non-adherence and they are thus the primary target of the trial. Multiple patients within one family will be excluded to prevent contamination within a family. Contamination is possible for the medications that need to be started in a timely fashion and thus they must be available at the clinics. The study team will audit mandatory stocking and dispensing records for medications stored on site to reduce contamination. Some prescribing contamination may occur in which a clinician prescribes medications from the list to control patients who have their usual access (i.e. patients will pay for the medications). Any contamination will tend to reduce the effect size (i.e., it will increase adherence in the control group and may reduce adherence in the intervention group). The low risk of contamination is one reason that we have decided to conduct an individual RCT rather than a cluster RCT which would involve a larger number of sites and be substantially more expensive.

Some patients may acquire public medication insurance during the follow-up period. All patients will be analyzed using the intention-to-treat method and the number of such patients in each arm will be reported.

### *2.5 What are the planned inclusion/exclusion criteria?*

#### *Inclusion criteria*

- Self-reported cost-related medication non-adherence in last 12 months. We will use phrasing used in the Canadian Community Health Survey and similar surveys in other countries: "In the last twelve months, did you not fill a prescription or do anything to make a prescription last longer *because of the cost*?"[5, 37]
- Age 18 or older.

#### *Exclusion criteria*

- Valid public medication insurance (Ontario Drug Benefit) card.
- Family member living at same address of patients already enrolled.
- Joined practice within last 6 months.

We will exclude patients who are new to the practice as patients joining the practice in order to participate in the study is a potential source of bias and because some secondary outcomes require baseline assessments that will not be available for new patients.

We will not exclude patients who are eligible for public medication insurance but who do not have such coverage (e.g. patients who have lost or cannot access their benefit card).

We will not exclude patients with private medication insurance as long as they answer “yes” to the first question in the inclusion criteria. 7 % of Canadians who have medication coverage still report cost-related nonadherence.[5] Private insurance often requires some out of pocket expenses. Individuals who have private insurance and are not experiencing cost-related barriers to medication adherence will not be enrolled as they will not meet the inclusion criterion.

#### *2.6 What is the proposed duration of the treatment period?*

The treatment period will be for 24 months for each patient.

#### *2.7 What is the proposed frequency and duration of follow up?*

The follow up period is identical to the treatment period (and so will also be 24 months for all participants). The 24 months of treatment and outcome assessment allows for the evaluation of clinical outcomes and cumulative costs adequately. Medication adherence and health outcomes data (blood pressure, HbA1c levels and cholesterol levels) will be collected during regularly scheduled appointments. Inappropriate prescribing, prescription records and costs will be reviewed from the electronic medical records.

#### *2.8 What are the proposed primary and secondary outcome measures?*

*Primary outcome:* Proportion (%) of patients who appropriately adhered to all prescribed treatments (i.e. were adherent to all prescriptions deemed appropriate).

*Secondary outcome:*

1. Proportion (%) of prescriptions that are appropriate.
2. Proportion (%) of prescriptions that are adhered to.
3. HbA1c levels in patients with diabetes (adjusted for baseline).
4. Blood pressure in hypertensive patients (adjusted for baseline).
5. LDL cholesterol levels in patients taking a statin (adjusted for baseline).
6. Per capita healthcare costs.

#### *2.9 How will the outcome measures be measured at follow up?*

We will use a combination of established methods for assessing the primary outcome: appropriate medication adherence, which requires assessment of both adherence and appropriateness [3]. Participants will be asked to complete a survey on the telephone between 9 and 12 months and between 21 and 24 months after randomization. If patients are not reached after 2 phone calls, they will be given the option to complete the survey by email and will also receive a letter in the mail requesting that they complete the survey. At this point, the

participant's clinician will be asked if there have been changes to contact information in a PSS message. The clinician will be asked to provide the patient with the telephone number that they can call in order to complete the survey. After these steps, if the patient has not completed the survey, they will be called again and given the option to complete the survey in person at the clinic, or in person at their home. For those who agreed to the home visit and it was not successful (for instance, the patient is not home or does not answer the door) a letter will be left at the home or mailed to the address to inform them we have tried to reach them and to remind them about the survey.

There is no "gold standard" measure of medication adherence because more invasive measures of adherence can change actual adherence. We will employ questionnaires, chart reviews and electronic monitoring as recommended and previously used in trials[38]. Standard and validated medication adherence questions will be completed by patients over the telephone, by email, or during their regularly scheduled clinic visits between 9 and 12 months and again between 21 and 24 months to determine the proportion of reported missed doses ("In the last week, how many times did you miss taking your regular medications?").[38] Self-reported non-adherence, taking into consideration the number of expected medication doses, greater than 80 % will be considered adherent (e.g. one or zero missed doses in one week for a medication taken once a day). While prone to memory bias as patients attempt to recall their adherence patterns[3], questionnaires are not as susceptible to social desirability bias as interviews due to anonymity[3, 38] and do not suffer from a drop in completion rates as a study progresses, as diaries do[39]. Chart reviews will be conducted by accessing electronic medical records (EMRs) to determine if long term medications are re-ordered when expected (i.e. for patients who are prescribed a three month supply of medication, evidence of written prescriptions every three months would indicate adherence) in a blinded fashion. Prescriptions written within 18 days of the expected renewal date (20 % of typical renewal period of 90 days) will be classified as adherent. While susceptible to pill dumping, like other objective measures such as pill counts[3], EMR reviews do not depend on recall. Electronic monitoring is considered by many the best method for measuring adherence and is the only method that can practicably provide daily dosage information[40]. However, given the high costs involved only a small subset of patients in the study will be measured in this way[40]. The device chosen for this study is the Medication Event Monitoring Systems (MEMs) device, as it is the most widely used[40]. If bottle openings to take medications take place greater than 80% of the times expected, a patient will be classified as adherent. Self-reporting has been shown to overestimate adherence[3] while electronic monitoring is prone to underestimation[40].

This combination of three methods for assessing adherence will be more rigorous than the single methods used in previous trials. [29, 48, 49]

Adherence will be treated as a dichotomous variable. Participants deemed non-adherent by any of the three methods will be classified as non-adherent for the primary analysis. We will also report adherence rates by each of the three measures for the intervention and control groups. Prescriptions for medications intended to be taken on an "as needed" basis (e.g. analgesics, salbutamol) will be excluded from the adherence analysis.

Prescribing appropriateness will be assessed by blinded assessors with access to patient electronic medical records including clinician notes. Two independent adjudicators will verify all prescriptions for appropriateness. Any disputes will be resolved by a third independent adjudicator. Assessors will review all prescriptions written to patients in control and intervention

arms using independently developed explicit patient level prescribing appropriateness indicators.[41] These indicators address the management of common chronic diseases such as heart disease, diabetes and asthma.[41] Prescribing appropriateness is a dichotomous variable and thus each prescription will be counted as appropriate or not appropriate.

The ***primary outcome of appropriate adherence*** will be determined by assessing the percentage of patients who were both adherent to all prescribed medications and received no inappropriate prescriptions.

#### *Secondary outcomes*

Adherence and appropriate prescribing will each also be secondary outcomes. For each, we will report the proportion of all prescriptions in each arm that meet the above criteria.

The mean change in HbA1c for patients with diabetes will be a secondary outcome. HbA1c levels will be mandatorily determined between 9 and 12 months and between 21 and 24 months after randomization in patients who had an HbA1c level measured no more than 6 months before randomization and who were prescribed a treatment for diabetes (e.g. metformin, gliclazide, or insulin). HbA1c is easy to assess, is routinely measured and is known to be associated with clinically important outcomes such as myocardial infarction and mortality[42].

The mean change in blood pressure for patients with hypertension or diabetes will be a secondary outcome. This will be assessed mandatorily between 9 and 12 months and between 21 and 24 months after randomization in patients who had a blood pressure reading recorded no more than 6 months before randomization and who are prescribed an antihypertensive treatment. Blood pressure is routinely measured and is known to be associated with clinically important outcomes such as myocardial infarction,[43] stroke[44] and mortality.[45]

The mean change in low density lipoprotein cholesterol (LDL) will be a secondary outcome. LDL will be determined mandatorily between 9 and 12 months and between 21 and 24 months after randomization in patients who had an LDL level measured within 12 months of randomization and who are prescribed a statin. LDL levels are routinely measured and known to be associated with clinically important outcomes such as myocardial infarction, stroke and mortality [46]. Reductions in LDL by statins and other treatments reduce the risk of death based on multiple statin trials and preliminary results from the IMPROVE-IT trial (ezetimibe-simvastatin versus statin) presented in November of 2014 [47].

HbA1c, blood pressure and LDL will be assessed by audits of the EMR.

Patient and community engagement are an important and large part of this study and separate funding has been obtained from St Michael's Hospital and the Toronto Central Local Health Integration Network for engagement around the development of intervention and the selection of outcomes. Briefly, patient, clinician and pharmacist concerns and experiences with the dispensing model will be collected using questionnaires, focus groups and one-on-one interviews. In addition, focus groups and patient panels organized in collaboration before, during and after the study will provide feedback on the intervention.

Health care costs will be measured using administrative data. Trial data from participants who explicitly consented to data linkage were linked with healthcare administrative data records from the Ontario Ministry of Health and Long-Term Care, held at the Institute for Clinical Evaluative Sciences. These data included detailed information from all acute care and psychiatric hospitalizations and emergency department visits in Ontario; claims for fee-for-service reimbursement from all physicians in Ontario; claims for prescription medications filled under the Ontario Drug Benefits program, which provides comprehensive medication insurance for all

Ontario residents aged  $\geq 65$ , as well as select younger patients (such as those on social assistance, requiring disability support programs, or with catastrophic drug expenses); and records of home care services. Because of the single-payer universal healthcare system in Ontario, all care is captured with no missing data. Using these data, we ascertained the following outcomes for 2 years after randomization: number of ambulatory visits with primary care physicians, number of ambulatory visits with specialist physicians, number of emergency department visits, number of hospitalizations, costs of ambulatory visits with primary care physicians, costs of ambulatory visits with specialist physicians, other physician costs including laboratory testing, costs of emergency department visits, costs of hospitalizations, costs of publicly-funded medications and costs of homecare. Costs of emergency department visits, hospitalizations and home care were only available to March 31, 2019, so these costs were slightly underestimated for the small proportion of patients whose follow-up time extended beyond that date.

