### **Outcomes**

*Primary outcome:* Proportion (%) of patients who appropriately adhered to all prescribed treatments (i.e. were adherent to all prescriptions deemed appropriate).

*Secondary outcome:*

1. Proportion (%) of prescriptions that are appropriate.
2. Proportion (%) of prescriptions that are adhered to.
3. HbA1c levels in patients with diabetes (adjusted for baseline).
4. Blood pressure in hypertensive patients (adjusted for baseline).
5. LDL cholesterol levels in patients taking a statin (adjusted for baseline).
6. Per capita healthcare costs.

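### The per capita healthcare cost outcome leaves out the trial's own medicines and all privately paid drug spending, and no payer perspective is stated

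*Supplement*

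**What the plan says.** Section 1.2 of the latest (24-month) protocol asks, as its sixth secondary question, whether the intervention lowers healthcare costs per head. Protocol 2.8 and the SAP of 9 September 2019 (Outcomes) both list the matching outcome: "Per capita healthcare costs".

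Protocol 2.9 (Secondary outcomes) gives the source: "Health care costs will be measured using administrative data". The drug data in that source are "claims for prescription medications filled under the Ontario Drug Benefits program", and the list of cost components ends with "costs of publicly-funded medications and costs of homecare". No other drug component appears. Linkage is limited: "Trial data from participants who explicitly consented to data linkage were linked". On completeness the section states: "Because of the single-payer universal healthcare system in Ontario, all care is captured with no missing data". It then says that emergency, hospital and home care costs were available only to 31 March 2019.

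Protocol 2.5 lists as an exclusion: "Valid public medication insurance (Ontario Drug Benefit) card". Protocol 2.2 has the trial supply listed medicines free to intervention patients, usually by mail every 90 days and with pharmacist counselling. Control patients keep their usual access.

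Protocol 2.10 separately plans to compare average drug cost per patient between arms. Protocol 2.7 and 2.14 say costs can be taken from the electronic medical record (EMR).

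**The concern.** The intervention is a supply of medicines. A cost outcome that can register fewer visits and admissions, but not the supply that may have produced them, does not answer whether the intervention lowers healthcare costs. The population adds to the problem: people already covered by the one drug program in the data are screened out at entry, so most drug spending in either arm may fall outside what is counted.

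Protocol 1.5 says the results are meant to inform decisions on public drug coverage. A reader who meets the cost result beside a statement of complete capture would reasonably take it as the full cost. Neither document states a payer perspective, and the SAP's Secondary outcomes section gives no method for costs, so nothing corrects that reading.

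**Working it through.** The documents give no figure for the cost outcome, so there is none to reproduce. The check has two parts: a comparison of the text, then an illustration of size.

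**Which drug costs are counted (Protocol 2.9 against 2.2 and 2.5)**

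| Drug cost | In the listed components? |
|---|---|
| Ontario Drug Benefit claims, either arm | Yes |
| Study-supplied medicines (intervention) | No |
| Dispensing, mailing and counselling (intervention) | No |
| Unlisted or controlled drugs bought privately (intervention) | No |
| Private-insurance or out-of-pocket drugs (control) | No |

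The completeness sentence fails on three counts. It is untrue for drugs, as the table shows. It does not hold for participants who declined linkage. And three components stop at a calendar date. The last two limits are disclosed on either side of the sentence, so the section contradicts itself rather than hiding them.

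**Size of the omission**

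Inputs:
- Follow-up for costs: 2 years (Protocol 2.9).
- Yearly drug cost per patient, D_I (intervention) and D_C (control): $477 to $771. These are the 2011 national averages for Sweden and Canada in Protocol 1.1. They are not trial data. D_C = 0 is added as an extreme.
- Share of drug cost appearing in public claims, s: assumed 0 to 0.25, the same in both arms. The documents give no value.

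Public-payer view, assuming that payer would fund the free medicines. Control private spending is not a cost to this payer, so the omission falls on the intervention arm:

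omitted = 2 × D_I × (1 − s)

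- D_I = 771, s = 0: 2 × 771 = $1,542
- D_I = 477, s = 0: 2 × 477 = $954
- D_I = 477, s = 0.25: 2 × 477 × 0.75 = $715.50, about $716

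All-payer view, where both arms have omitted costs:

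net omitted = 2 × (D_I − D_C) × (1 − s)

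- D_I = 477, D_C = 771, s = 0: 2 × (−294) = −$588
- D_I = D_C: $0
- D_I = 771, D_C = 477, s = 0: 2 × 294 = +$588
- D_I = 771, D_C = 0, s = 0: 2 × 771 = +$1,542

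A positive value means the intervention's relative cost is understated; a negative value means it is overstated.

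The public-payer formula treats all drug cost outside public claims as supplied by the trial. Controlled substances and unlisted drugs are not supplied (Protocol 2.2), and uptake is assumed at 90% (SAP, Sample size calculation); both would lower the figure. Dispensing, mailing and counselling would raise it.

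**The case against.** The strongest reply is that the plan does not ignore drug costs. Protocol 2.10 compares them by arm and uses that comparison, not the administrative total, to project the cost of wider adoption. This stands, and a reader who inferred that the plan leaves drug costs unstudied would be wrong. What remains is that 2.10 is not joined to outcome 6 and gives neither unit prices nor a costing method for trial-supplied medicines.

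A reader might also infer that the intervention is bound to look cheaper than it is. The documents do not support that without a stated perspective. Control private and out-of-pocket spending is missing too, and Protocol 1.1 suggests that a short list might cost much less.

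Nor do the documents show that public drug claims will be close to zero in both arms. The card exclusion applies at entry, and Protocol 2.4 expects some participants to gain public coverage during follow-up. This softens the point without removing it. If such an intervention patient went on taking study medicines, no public claim would arise, while a control patient's fill would produce one. That difference would be a shift of budget, not a saving.

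The date cut-off is disclosed as a slight underestimate affecting few participants, and nothing suggests that it differs by arm. Finally, this is the sixth secondary outcome, the SAP treats its secondary analyses as supportive or exploratory, and Protocol 2.9 lists costs by component without defining a sum. These points bear on severity and are accepted.

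**Conclusion.** The concern holds in this form: outcome 6 as specified excludes the cost of the medicines and services under test and all non-public drug spending in both arms, and its claim of complete capture is incorrect.

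If the public payer would bear the cost of the free medicines, the omission favours the intervention. The range of $716 to $1,542 per intervention patient over 2 years shows scale only; it rests on 2011 national averages and an assumed share in public claims. Counting all payers, the illustration runs from −$588 to +$1,542, so neither direction nor size can be settled from the documents.

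This is a should-fix. The primary outcome, the sample size and the clinical secondary outcomes are untouched, but the healthcare-cost question cannot be answered from the listed components alone.

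**What to change.** 1. State the payer perspective for outcome 6 in both the protocol and the SAP.
2. For a public-payer total, add study-supplied medicines and their dispensing, counselling and mailing, priced from pharmacy dispensing records. For an all-payer total, also add drug costs in both arms priced from EMR prescriptions, counting each medicine once. State the unit prices and link this explicitly to Protocol 2.10.
3. If these costs are not added, rename the outcome *publicly funded healthcare costs excluding study medicines*, and do not conclude from it alone that the intervention reduces healthcare costs.
4. Delete or qualify the completeness sentence, and report the number linked in each arm.

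The cost is modest pricing work and some wording, with no new data collection from patients. The audit in Protocol 2.4 covers only stock held at the clinics, so records for mailed medicines would have to come from the dispensing pharmacies. The public-payer result is likely to become less favourable to the intervention.
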